**Fig. 1 Fig1:**
[figure not shown]
Standard Protocol Items: Recommendations for Interventional Trials (SPIRIT) flowchart

**Fig. 2 Fig2:**
[figure not shown]
Diagram of the steps of data collection

### Safety protocols

To prevent cross-contamination, the team responsible for data collection will perform hand hygiene before and after the procedures; all equipment that comes into contact with the patients will be disinfected with 70% ethyl alcohol [41]; and after each music listening session, the disposable headphone protectors will be replaced.

During the pandemic period for the new coronavirus, all biosafety protocols will be strictly followed, and the data collection team will use all appropriate personal protective equipment, such as N95 masks, face shields, disposable aprons, gloves, and caps. Patients will also wear disposable masks during collection in the pre- and postoperative period.

As for adverse events, their occurrence is not predictable in this research, given the nature of the intervention and the lack of description in the literature of adverse events resulting from listening to music. However, in the event of any complications or adverse events for the participants, the information will be recorded and the Research Ethics Committee will immediately be notified.

### Evaluated outcomes

#### Primary outcome

Preoperative anxiety-state: Refers to the average reduction (difference) in anxiety-state scores, obtained after subtracting the scores, before and after intervention or standard care, in both groups (experimental and control), in the immediate preoperative period.

#### Secondary outcomes

Systolic blood pressure: Refers to the mean reduction (difference) between the values of systolic blood pressure, obtained after subtracting the values, before and after intervention or standard care, in both groups (experimental and control), in the immediate preoperative period and on the first postoperative day;Diastolic blood pressure: Refers to the mean reduction (difference) between the values of diastolic blood pressure, obtained after subtracting the values, before and after intervention or standard care, in both groups (experimental and control), in the immediate preoperative period and on the first postoperative day.Heart rate: Refers to the average reduction (difference) between the heart rate values, obtained after subtracting the values, before and after intervention or standard care, in both groups (experimental and control), in the immediate preoperative period and on the first postoperative day;Respiratory frequency: Refers to the average of the reduction (difference) between the respiratory frequency values, obtained after subtracting the values, before and after intervention or standard care, in both groups (experimental and control), in the immediate preoperative period and on the first postoperative day;Oxygen saturation: Refers to the average increase (difference) between the oxygen saturation values, obtained after subtracting the values, before and after intervention or standard care, in both groups (experimental and control), in the immediate preoperative period and on the first postoperative day;Postoperative pain: Refers to the mean reduction (difference) of pain scores at rest and when instructed to cough, obtained after subtracting the scores, before and after intervention or standard care, in both groups (experimental and control), on the first postoperative day.

### Statistical methods

#### Sample size

The sample size calculation was performed by a statistician without clinical involvement in the research and obtained after conducting the pilot study, using the Power Analysis and Sample Size (PASS) version 13.0 software. It should be noted that the participants in the pilot study will not be part of the main study. A type I error *α* = 0.05 and a type II error *β* = 0.2 were considered, reaching a statistical power of 80%.

For the pilot study, 13 patients were analyzed, 7 patients from the control group and 6 from the experimental group. The specific objective no. 1 was used to determine the sample size and, considering preoperative anxiety-state as the primary outcome, the mean reduction in the STAI-State scores for the experimental group was 5.67 points (standard deviation: 5.89), and for the control group, it was 3.00 points (standard deviation: 7.30). Based on these values, the sample size calculated is 196 participants, that is, 98 per group.

The estimated dropout rate (loss to follow-up) is 27.8%, considering the data obtained in the pilot study. The sampling loss will be included in a randomization list, and if there is attrition in either of the two evaluated groups, new participants will be included based on this list, until the loss is exhausted. It should be noted that if additional participants are to be randomized to maintain the sample size, each new participant will be randomly assigned to one of the groups with the same original allocation ratio (1:1).

#### Statistical analysis

The collected data will be entered in a Windows® Excel® spreadsheet, using the double entry technique, for later validation. The identification of each study participant, as well as their allocation group, will be done using codes. Then, the validated database will be imported into the Statistical Package for the Social Sciences (SPSS) version 21.0 for processing and analysis.

The normality of the data will be verified by the Kolmogorov-Smirnov test or by the Shapiro-Wilk test. To test the hypothesis of homogeneity of the two groups (experimental and control), when applicable, Student’s *t*-test will be used for independent samples in quantitative variables and the chi-square test of homogeneity for categorical variables.

The univariate exploratory analysis of the data will be performed by the distribution of absolute and relative frequency for categorical variables and measures of central tendency (mean and median) and of variability (amplitudes and standard deviation) for quantitative variables.

To compare the anxiety-state scores, cardiorespiratory parameters, and pain intensity scores, at rest and when instructed to cough, between the experimental and control groups, Student’s *t*-test for independent samples will be used, when applicable.

To compare the anxiety-state scores, cardiorespiratory parameters and pain intensity scores, at rest and when instructed to cough, within each group, experimental and control (intra-group analysis), a paired *t*-test will be used, when applicable.

Subgroup analysis will be performed and, if there is a violation of homogeneity of the groups for one or more confounding variables, a corresponding post hoc multivariate analysis will be performed.

To check the correlation between preoperative anxiety-state and intensity of postoperative pain, Pearson's correlation coefficient will be used, if applicable.

This research will consider a level of significance of *α* = 5% and a confidence interval of 95%. The data will be presented in tables and figures.

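### Normality is checked by either of two tests and the between-group t-test is conditional, so the primary method is not fixed and may not match the mean reduction that the outcomes define

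*Protocol article*

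**What the plan says.** Protocol article, Statistical analysis: "The normality of the data will be verified by the Kolmogorov-Smirnov test or by the Shapiro-Wilk test". The section does not say which test is to be used when, at what level, on which variable, or whether by arm or pooled. The comparison that serves the primary and all secondary outcomes follows: "between the experimental and control groups, Student’s *t*-test for independent samples will be used, when applicable". The within-group comparison and the correlation are hedged in the same way: "a paired *t*-test will be used, when applicable" and "Pearson's correlation coefficient will be used, if applicable". Applicability is not defined and no alternative test is named.

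The outcomes themselves are defined as means. Primary outcome: "Refers to the average reduction (difference) in anxiety-state scores, obtained after subtracting the scores, before and after intervention or standard care". Secondary outcomes, for pain: "Refers to the mean reduction (difference) of pain scores at rest and when instructed to cough". The cardiorespiratory outcomes are also defined as mean differences. The Sample size section plans 98 per group from the pilot mean reductions and standard deviations.

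**The concern.** A confirmatory trial needs its main comparison settled before the data are seen. Here the only distributional check described is a normality test, and the tests that follow are conditional. The natural reading is that a failed check removes the t-test.

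Two things then remain open. The first is whether the t-test is run at all. That depends on the observed data and on which normality test the analyst picked. STAI-State and the pain scale give whole-number, bounded scores, and with about 98 per arm a normality test can reject for rounding or skew that does little harm to a comparison of means. The second is what the main result would estimate. If the replacement were a rank test, it would no longer address the mean reduction that the outcome sections define and on which the trial was sized.

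**Working it through.** **1. What the sample size assumes.** Inputs from the Sample size section: reductions of 5.67 (SD 5.89) and 3.00 (SD 7.30), α = 0.05, power 80%.

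- Difference: 5.67 − 3.00 = 2.67.
- Average SD: √[(5.89² + 7.30²)/2] = √43.99 = 6.63.
- Normal approximation: n = 2(1.96 + 0.8416)² × 43.99/2.67² = 96.9, so 97 per arm.
- Noncentral t: power is 0.797 at 97 and 0.801 at 98, so 98 per arm, as stated. A one-sided test would need 77.

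The stated size therefore reproduces as a two-sided t-test on means, with no condition attached.

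**2. How often a normality check would fail.** Simulation with 98 per arm and 1,000 to 2,000 trials per scenario. A check fails if normality is rejected at 5% in either arm. The level and the by-arm testing are assumptions. Kolmogorov-Smirnov (KS) is shown with and without the Lilliefors correction, because the document does not say which is meant. The STAI-State change has the pilot-sized SD (about 6.6) and is rounded to whole points. The document gives no pain distribution, so a range was assumed: baseline mean 2 to 7, baseline SD 2 to 2.5, mean change 0.5 to 2, SD of change 1 to 3, all rounded and truncated to 0-10.

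| Change score | Shapiro-Wilk | KS, Lilliefors | KS, uncorrected |
|---|---|---|---|
| STAI-State, normal | 12-13% | 33-37% | under 1% |
| STAI-State, heavy-tailed (t, 5 df) | 84% | 81% | 11% |
| STAI-State, skewed (gamma, shape 4) | 100% | 99% | 40% |
| Pain, SD of change 1 to 1.5 | 100% | 100% | 99-100% |
| Pain, SD of change 2 | 99-100% | 100% | 65-93% |
| Pain, SD of change 2.5 | 91-96% | 100% | 36-52% |
| Pain, SD of change 3 | 72-79% | 99% | 22-24% |

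For the normal STAI-State change, Shapiro-Wilk and Lilliefors KS reach different answers in 27-31% of trials. For the heavy-tailed change, Shapiro-Wilk and uncorrected KS differ in about 72%.

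**3. Whether the check protects the error rate.** With no true effect, the t-test used unconditionally has a simulated type I error of 4.7-5.2% for STAI-State (normal, heavy-tailed or skewed) and 4.4-5.7% for pain. The two-stage rule (t-test if normality is not rejected, otherwise Mann-Whitney, which is an assumed fallback) gives 4.5-5.4%. Picking the more favourable of the two normality tests gives at most 5.5%. With 2,000 trials the simulation standard error near 5% is √(0.05 × 0.95/2000) = 0.5 points.

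**4. Power at the planning effect.** Under normality the two-stage rule gives 0.79-0.80, the same as the t-test alone. Under the heavy-tailed and skewed shapes it gives 0.86-0.90, because the rank test is then usually the one run. The t-test alone gives 0.79-0.80.

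**The case against.** The text never says that a failed normality test rules out the t-test. The same hedge covers the homogeneity sentence, which includes the chi-square test, where normality is irrelevant, so it may be no more than a general caution. No rank test is mentioned; a fallback could be a transformation, an unequal-variance t-test or a bootstrap, some of which may keep the comparison of means. Naming the fallback may properly be left to a fuller protocol or analysis plan. These points stand: the link to normality and the switch to ranks are inferences. But if applicability means something other than normality, it is undefined, and the main test is still not fixed.

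A reader might go further and infer three things that the documents do not support.

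- **That pain would almost never be tested as defined.** This rests on an assumed distribution. With uncorrected KS and an SD of change of 3, the t-test would survive in more than three quarters of simulated trials.
- **That the mean reductions would not be reported.** The section plans means, medians and standard deviations, and mentions a 95% confidence interval.
- **That the procedure inflates type I error.** Always taking the smaller of the t and rank p-values gave 5.6-6.1% (simulation error about 0.6 points), but the document describes no such rule.

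The rounding effect on Shapiro-Wilk is also small. Two arms tested at 5% would fail at least once in 1 − 0.95² = 9.75% of trials under exact normality, against 12-13% here.

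**Conclusion.** The point holds in a limited form. The document offers two normality tests with no rule for choosing and makes the between-group t-test conditional. On the natural reading, the method for the primary and secondary outcomes depends on the data and on the analyst's choice of check. That choice can change the answer: for a truly normal STAI-State change, the failure rate runs from under 1% to about 37% across the candidate tests.

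The harm is an unfixed primary method and, if the fallback is a rank test, a main result that does not match the defined mean reduction or the basis of the sample size. No material effect on type I error was found, and no loss of power. The condition also protects nothing, since the t-test holds its level at this sample size without it.

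The STAI-State figures rest on the assumed shapes and the pilot SDs, and the pain figures on assumed distributions throughout. The missing name of a fallback is not the defect; the data-driven, two-option condition is what this document itself sets badly.

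**What to change.** Drop the normality condition for between-group comparisons. State one analysis for STAI-State and each secondary outcome, whatever the distribution: the difference in means with a 95% confidence interval. It should preferably come from a linear model of the after-session score with the before-session score as covariate, since both are already collected. The baseline adjustment is a preference; the planned t-test, made unconditional, would also cure the problem. Keep normality checks and a rank test as named sensitivity analyses only.

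The cost is analysis wording: no extra patients or data, and the 98 per arm stands. The downside is losing the freedom to make a rank test the main result, including its higher rejection rate under the heavy-tailed or skewed shapes simulated above.

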### Randomization, concealment of allocation, and masking

Study participants will be randomly allocated, in a 1: 1 ratio, to one of the groups, experimental (with music listening) or control (without music listening). The randomization scheme will be generated by using the website Randomization.com (http://randomization.com).

After randomization, a list will be generated, numbered sequentially, for the allocation of participants to the research groups. To ensure concealment of the allocation, the groups to which participants are assigned, according to the generated list, will be inserted in opaque envelopes and numbered sequentially. These envelopes will be sealed and stored in a safe place. They will only be opened by the statistician, at the time of application of music listening or standard care for the corresponding participants. The entire process of randomization and concealment of the allocation will be carried out by the statistician, who will have no clinical involvement in the study.

The clinical trial will be conducted with simple masking, since the researchers responsible for applying the data collection instrument and measuring the variables studied, as well as the surgical and the prescribing teams, will be masked as to the allocation group of each patient. However, due to the nature of the intervention, it will not be possible to mask the research participants, considering that they will be aware of being part of the experimental group, while they are submitted to listening to music.

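### The primary comparison leaves the pre-session STAI-State score unused as a covariate and names scores where the outcome and sample size are on the reduction; a baseline-adjusted ANCOVA would gain power for free

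*Protocol article*

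**What the plan says.** - **Outcome.** The Primary outcome section defines preoperative anxiety-state as "the average reduction (difference) in anxiety-state scores, obtained after subtracting the scores, before and after intervention or standard care".
- **Sample size.** The Sample size section uses the same variable. In the pilot, "the mean reduction in the STAI-State scores for the experimental group was 5.67 points (standard deviation: 5.89"); the corresponding control figures were 3.00 and 7.30. The result is given as "the sample size calculated is 196 participants, that is, 98 per group". The section says that specific objective 1 was the basis, and that objective speaks of comparing scores.
- **Test.** The between-group sentence in Statistical analysis, beginning "To compare the anxiety-state scores, cardiorespiratory parameters, and pain intensity scores, at rest and when instructed to cough, between the experimental and control groups", prescribes Student's t-test for independent samples, when applicable. It names no covariate.
- **Adjustment.** The same section foresees a post hoc multivariate analysis if the groups prove not to be homogeneous on one or more confounding variables. It also plans a Kolmogorov-Smirnov or Shapiro-Wilk test, but states no rule for what follows from its result.
- **Baseline data.** Under Data collection instrument and Recruitment and data collection procedures, STAI-State is taken in both groups before and after the session. Under Randomization, concealment of allocation, and masking, the envelopes are opened only when music or standard care is about to be applied.

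**The concern.** Two things stand out. First, the outcome and sample size sections use the reduction, while the analysis section and objective 1 use scores. An analyst holding only the analysis section could test a different variable from the one that was powered.

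Second, neither an unadjusted t-test on the reduction nor one on post-session scores makes full use of the pre-session score. The first fixes the slope of after on before at 1, and the second fixes it at 0. ANCOVA estimates the slope from the data. The pre-session score precedes disclosure of allocation, so it is a proper baseline covariate. At stake are precision on the only powered endpoint and the extent to which chance baseline imbalance carries into the estimate.

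**Working it through.** **Inputs from the Sample size section.** Mean reductions 5.67 (SD 5.89) and 3.00 (SD 7.30); alpha 0.05; power 80%; 98 per group. Sidedness is not stated.

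**Step 1: reproduce the plan's figure.**
- Difference = 5.67 − 3.00 = 2.67.
- SD of the reduction = √((5.89² + 7.30²)/2) = √((34.69 + 53.29)/2) = 6.63.
- Two-sided alpha 0.05, non-central t: 98 per group, power 80.1%. The normal approximation gives 97. A one-sided test gives 77 and does not reproduce the figure.

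The stated size is therefore that of a two-sided t-test on the reduction.

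**Step 2: relate the three analyses.** Let r be the before-after correlation within groups, and assume equal before and after SDs, σ. Neither r nor σ is given in the protocol.
- Variance of the reduction: 2σ²(1 − r).
- ANCOVA residual variance: σ²(1 − r²).
- Ratio of ANCOVA to reduction: (1 + r)/2, so ANCOVA SD = 6.63 × √((1 + r)/2).
- SD of a single post-session score: 6.63/√(2(1 − r)).

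**Step 3: power by non-central t, difference 2.67.** The ANCOVA columns allow for one lost degree of freedom.

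| r (assumed) | ANCOVA SD | ANCOVA power at 98 per group | ANCOVA n per group for 80% | t-test on reduction, power at 98 | t-test on post-session score, power at 98 |
|---|---|---|---|---|---|
| 0.3 | 5.35 | 93.5% | 64 | 80.1% | 91.3% |
| 0.5 | 5.74 | 89.9% | 74 | 80.1% | 80.1% |
| 0.6 | 5.93 | 88.0% | 79 | 80.1% | 70.8% |
| 0.7 | 6.11 | 86.0% | 84 | 80.1% | 58.4% |
| 0.8 | 6.29 | 84.0% | 89 | 80.1% | 42.6% |
| 0.9 | 6.46 | 82.0% | 93 | 80.1% | 24.1% |

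**Step 4: chance imbalance, illustrated at r = 0.7.**
- Single-score SD = 6.63/√0.6 = 8.56.
- Standard error of the baseline difference = 8.56 × √(2/98) = 1.22 points.
- An imbalance of one standard error shifts the estimate from the reduction by (1 − 0.7) × 1.22 = 0.37 points, or 14% of 2.67.
- It shifts a post-session comparison by 0.7 × 1.22 ≈ 0.86 points, or 32%.
- ANCOVA adjusts for this imbalance.

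**The case against.** The best reply is that the protocol largely settles which variable is meant. The Primary outcome section defines the reduction. The Sample size section says it rests on objective 1, which speaks of scores, and then uses mean reductions; so the authors appear to treat comparing scores as comparing reductions. The stated 98 per group reproduces on that reading. Under randomisation the t-test on the reduction is valid and has the power that was planned. This stands, and it limits the point to clearer wording and a better method.

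A reader might go further and infer that the trial will test raw post-session scores and is therefore underpowered. The text does not support that. The analysis section never says post-session, and the outcome and sample size sections point away from it. Even on that reading, under the equal-SD assumption, power drops below 80% only when r exceeds 0.5; at r = 0.3 it would be 91%.

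A reader might also say that a change score always over-corrects for baseline when r is below 1. That needs equal before and after SDs, because the relevant slope is r × SD(after)/SD(before).

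Finally, the protocol does plan an adjustment for imbalance. It is conditional and post hoc, so the model would depend on the observed data. It does not replace a covariate named in advance.

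Nor can the point be left to an unseen analysis plan: the article itself fixes an unadjusted test, and its wording does not match its own outcome definition.

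**Conclusion.** The point holds as a free improvement plus a clarification of wording. It does not correct an error: the sample size is right for a two-sided t-test on the reduction, and no planned power is lost if that test is used. Baseline-adjusted ANCOVA would raise power at 98 per group from 80% to between about 94% (r = 0.3) and 82% (r = 0.9). Against the t-test on the reduction the gain is thus some 14 percentage points at the low end of that range and 2 at the high end.

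These figures rest on the pilot means and SDs, an assumed r and equal before and after SDs. The direction of the result is firmer than its size: apart from one degree of freedom, negligible with 196 participants, ANCOVA is not less precise than either unadjusted test. The mismatch between scores and reduction should be removed in any case, because the two readings give different tests.

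**What to change.** - State the primary analysis as an ANCOVA of post-session STAI-State on allocated group and pre-session STAI-State, reporting the adjusted mean difference with its 95% confidence interval. The group effect is the same as for the reduction adjusted for baseline, with the sign reversed, so the outcome definition can stay.
- Say that this model is fitted whatever the normality and homogeneity tests show. With 98 per group, robust standard errors can be used if needed.
- Use the same model for the preoperative cardiorespiratory outcomes.
- Keep the independent-samples t-test as a supportive analysis, worded explicitly as on the before-minus-after reduction, so that it ties back to the sample size. Align objective 1 with that wording.

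The cost is about one paragraph of text and one degree of freedom. No new data or participants are needed, and the target of 98 per group can stay. The change should go through the amendment route described under Ethical aspects before any data are analysed by group.
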